# Clinical and cost effectiveness of a parent mediated intervention to reduce challenging behaviour in pre-schoolers with moderate to severe intellectual disability (EPICC-ID) study protocol: a multi-centre, parallel-group randomised controlled trial

**DOI:** 10.1186/s12888-020-2451-6

**Published:** 2020-01-30

**Keywords:** Intellectual disabilities, Challenging behaviour, Randomised control trial, Stepping stones triple P, SSTP, Parenting interventions

## Abstract

**Background:**

Children with intellectual disabilities are likely to present with challenging behaviour. Parent mediated interventions have shown utility in influencing child behaviour, although there is a paucity of UK research into challenging behaviour interventions in this population. NICE guidelines favour Stepping Stones Triple P (SSTP) as a challenging behaviour intervention and this trial aims to evaluate its clinical and cost effectiveness in preschool children with moderate to severe intellectual disabilities.

**Methods:**

This trial launched in 2017 at four sites across England, with the aim of recruiting 258 participants (aged 30–59 months). The Intervention Group receive nine weeks of SSTP parenting therapy (six group sessions and three individualised face to face or telephone sessions) in addition to Treatment as Usual, whilst the Treatment as Usual only group receive other available services in each location. Both study groups undergo the study measurements at baseline and at four and twelve months. Outcome measures include parent reports and structured observations of behaviour. Service use and health related quality of life data will also be collected to carry out a cost effectiveness and utility evaluation.

**Discussion:**

Findings from this study will inform policy regarding interventions for challenging behaviour in young children with moderate to severe intellectual disabilities.

**Trial registration number:**

Clinicaltrials.gov, NCT03086876. Registered 22nd March 2017, https://clinicaltrials.gov/ct2/show/NCT03086876.

## Background

Intellectual Disability (ID) is a lifelong condition characterized by limitations in cognitive ability and adaptive behaviours identifiable from early childhood [1]. A report by the Challenging Behaviour Foundation in 2014 estimated that approximately 10,000 children with ID in the UK show challenging behaviour [2]. Challenging behaviour is defined as actions of such intensity, frequency and duration that it threatens the physical safety of a person or others around them [3]. Behaviours include self-injury, physical aggression and non-person directed behaviour such as property destruction [4]. Whilst challenging behaviour is reported to persist over time, only a small percentage of participants receive intervention [5].

Early intervention has been particularly influential in the improvement of longer term outcomes in children with conduct or behavioural disorders [6–11]. Health Economists have also demonstrated the cost benefit of interventions experienced in the preschool years, given that the early years are the time of maximum brain development, and also of maximum malleability [12–16]. Einfeld and colleagues [17] showed that challenging behaviour increases care costs, which may be prevented with affordable early intervention programmes.

Despite promising evidence from a number of parent mediated interventions with children in the general population (e.g. Sure Start, Video Feedback Sensitive Discipline, and Triple P- Positive Parenting Programme) [18], there is a paucity of UK based early intervention research for reducing challenging behaviours in young children with ID. Most existing interventions have been developed for children with behavioural problems with no specificity to ID.

NICE guidelines (advised by the parent members of the guideline development group) indicated that parenting interventions particularly Stepping Stones Triple P (SSTP), an adapted version of Triple P (TP), demonstrate sufficient evidence in reducing challenging behaviour in children with ID [19]. TP (and SSTP) is a system of psycho-educational and behavioural approaches that aim to increase parental confidence and skills so that parents are able to manage the child’s behaviour effectively. SSTP comprises different levels depending on increasing family complexity, with Level 4 recommended for parents of children with severe behavioural problems. Efficacy trials outside the UK have indicated significant reductions in challenging behaviour in children with ID [20]. Although there is a scarcity of economic data for SSTP itself, trial and observational data from a number of countries suggest delivery of TP may be cost-effective, especially if it were applied at population levels [21, 22].

### Aims

This study aims to evaluate the clinical and cost effectiveness of Level 4 SSTP in a multi-site parallel cluster randomised control trial of preschool children with moderate to severe ID 12 months post randomisation. Treatment as usual (TAU) is available to participants in both arms of the trial.

The primary hypothesis is that the addition of level 4 SSTP to TAU will reduce challenging behaviour on completion of the intervention at 12 months post randomisation, compared to TAU alone. The primary outcome is the severity of challenging behaviour using the parent completed preschool Child Behaviour CheckList (CBCL) [23].

The secondary hypotheses include:
SSTP will reduce challenging behaviour measured at 12 months post randomisation in blind rated observations and caregiver/teacher questionnaire measures.SSTP will be more cost-effective compared to TAU.

## Method

### Trial design and setting

The randomised control trial is parallel and two-armed with blinding of outcome assessors. It includes a process evaluation with parent qualitative interviews to enhance understanding of the appropriateness and feasibility of the intervention. The study was planned and implemented in accordance with the Consolidated Standards of Reporting Trials (CONSORT) extension standards to compare the cost-effectiveness of the combination of SSTP plus TAU, versus TAU alone in reducing challenging behaviour at 12 months post randomisation. The trial design is summarised in Fig. 1.

**Fig. 1 Fig1:**
[figure not shown]
Flow chart of the study design. This chart demonstrates the flow of participants through the trial from initial contact to the completion of the follow-up assessments

Study participants are recruited from a wide variety of services within the participating centres in North and South London, North East (Newcastle and surrounding areas) and North West England (Blackpool and surrounding areas). Services include NHS settings, e.g. Child Development Teams; Child and Adolescent Mental Health Services; education (nursery/preschool) and third sector organisations e.g. caregiver groups. A number of Participant Identification Centres have also been opened (Table 1).

**Table 1 Tab1:** List of recruitment sites and participant identification centres

Site	Participant Identification Centres (PICs)
Blackpool Teaching Hospitals NHS Foundation Trust	None
Central and North West London NHS Foundation Trust	Royal Free London NHS Foundation Trust
	Imperial College Healthcare NHS Trust
	Great Ormond Street Hospital NHS Foundation Trust
	Primary Care (Islington/Camden GP practices, Barnet CCG practices, Enfield CCG practices)
Guy's and St Thomas' NHS Foundation Trust	St George’s University Hospital NHS Foundation Trust
	Lewisham and Greenwich NHS Trust
Cumbria, Northumberland, Tyne and Wear NHS Foundation Trust	Northumbria Healthcare NHS Foundation Trust
	South Tyneside and Sunderland NHS Foundation Trust
	Newcastle upon Tyne Hospitals NHS Foundation Trust
	Gateshead NHS Foundation Trust

**Note:**
*CCG* Clinical Commissioning Groups

#### Eligibility criteria

Parents of young children concerned about their child’s behaviour within the four participating centres are eligible for inclusion in the study if:
Parents are at least 18 years of age.Child is aged 30–59 months at identification.Child has moderate to severe ID (parent reported Adaptive Behaviour Assessment System (ABAS) General Adaptive Functioning score of 40–69) [24].Reports of challenging behaviour over a 6- month period but no less than 2 months.

Exclusion Criteria
Child has mild, profound or no ID on parent reported ABAS.Parent/carer has insufficient English language to complete study questionnaires.Another sibling is taking part in the study.

#### Participant identification and screening

Eligible participants are identified by the community paediatric and child and adolescent mental health teams in each of the four areas. Health or social care professionals identify eligible participants through new referrals or existing cases. Identification involves reviewing or screening identifiable personal information of participants by members of the regular clinical team. A member of clinical staff/clinical study officer contacts eligible participants, gives an introduction to the study and the study Patient Information Sheet. All participants who are interested in taking part complete an Expression of Interest form which is then passed on to the researchers.

Parents need to consent to the screening process, including the parent administered ABAS about the child’s adaptive behaviour/level of functioning. This determines whether a child’s level of intellectual ability falls within the inclusion criteria, and confirms that the child has had challenging behaviours continually in the past two months, i.e. such behaviours being present several times a week. Where the child fulfils the adaptive function range, the baseline assessment (assuming consent is given) takes place following which the participant is randomised either to the intervention arm (SSTP plus TAU) or TAU.

#### Interventions

##### SSTP plus TAU

Level 4 Stepping Stones Triple P is a 9 week psycho-education programme with 6 group sessions and three individual telephone or face to face contact with participants. SSTP is an adapted parenting programme for children with ID. The sessions cover strategies that parents can use to reduce unwanted behaviours, maintain behavioural change, cultivate a positive relationship with their child and facilitate independent problem solving. Each group session lasts approximately 2.5 h and individual sessions last about 30 min. Parents receive a course book with topics to be covered in each session and are contacted by the therapist if a session is missed.

##### Treatment fidelity

Each therapist (eight: two per centre) responsible for delivering SSTP has been trained in the Stepping Stones Training and Accreditation programme. Therapists were observed by TP trainers to build therapist competence and are provided with monthly supervision to ensure fidelity of the intervention and ongoing support and skills maintenance as is appropriate for psychosocial interventions [25]. Further, to determine whether treatment was delivered as intended (adherence), each therapist completes individual session checklists and all the sessions are videotaped to be rated by independent assessors (competence). A random 10% of assessments is double rated for reliability by an external blinded expert. Therapist deviations from the manualised intervention will be recorded to examine where flexibility may be required based on individual participant needs.

##### Treatment as usual

Parents continue to access interventions and therapies on offer to them in their local area, including a range of services such as support from health visitors, primary care engagement and advice, early intervention provided by community paediatric services or Child and Adolescent Mental Health Services, and parenting advice and support sessions by carers’ groups or other third sector organisations. It includes evidence based treatments (e.g. Webster Stratton Incredible Years, Early Bird and Strengthening Families interventions), support groups by third sector and voluntary groups (e.g. the charity Contact and locally organised parent groups) and via the NHS, which provides psychological and behavioural therapies as part of professional care (please see Additional File 1 for a more comprehensive list of available interventions). Parents allocated to both arms of the trial also receive a list of national resources and the Contact guide to challenging behaviour with tips and advice on social and health care supports.

#### Outcome measures

Outcomes are measured by self-report, direct parent-child observations and face-to-face interviews (See Table 2 for list of measures). All participants are assessed at the following time points: screening (T1), baseline (T2), four months post-randomisation (T3) and 12 months post-randomisation (T4). The assessment window for follow-ups is four weeks. Data collected outside these time windows will be recorded but not used for the main analyses (see Table 3 for the schedule of assessments at each time point).

**Table 2 Tab2:** List of study outcome measures

Outcome	Measure details
Primary outcome measure: Child Behaviour Checklist (CBCL)	Each question relates to a specific behaviour and is measured on a 3-point Likert Scale. Overall scores are derived for behavioural difficulties, attention problems and aggression. A T-score of Total Problem Behaviours of 60 or over signifies borderline to clinical caseness. CBCL incorporates DSM-5 diagnostic categories which rate comorbidities, e.g. autism spectrum disorders, mood disorders.
Mullen Scales of Early Learning	Assesses child level of disability [26]. Only assessed during the baseline assessment.
Revised Family Observation Schedule (FOS-RIII)	FOS-RIII is an objective measure of parent-child interaction, previously used in studies investigating SSTP and codes 20 min (four 5-min consecutive sections) home based videotaped parent-child interactions [27]. There will be an inter-rater reliability exercise on a proportion of the observations to ensure reliability.
Child Behaviour Checklist Caregiver-Teacher Report Forms (C-TRF)	Most children in the sample age range will have additional care outside the parental home allowing us to have additional perspectives on the child’s behaviour. The CBCL and C-TRF are extensively used to measure child’s behaviour and there are positive reports about high completion rates by teachers/nursery staff as shown in other studies [28].
General Health Questionnaire (GHQ)	Common psychiatric morbidity in the parent will be assessed at baseline, 4-month and 12-month follow-up.
Questionnaire on Resources and Stress (QRS-F short form)	Measures parental stress in caregivers of chronically ill or children with ID at baseline, 4-month and 12-month follow-up [29].
Caregiving Problem Checklist-Difficult Child Behaviour	The frequency of difficult child behaviour when the parent is completing care-giving tasks will be measured at baseline, 4-month and 12-month follow-up. Internal consistency is adequate (α = .78) [30].
Parenting Sense of Competence Scale (PSOC)	Assesses Satisfaction and Efficacy competencies as a parent at baseline, 4-month and 12-month follow-up [31]. Internal consistency for the measure ranges from α = .70–.80 [31].
Child and Adolescent Service Use Schedule (CA-SUS)	A modified version will be used in the trial to assess child health and social care service use at baseline, 4-month and 12-month follow-up [32].
Paediatric Quality of Life (PedsQL)	Assesses health related quality of life. The measure covers Physical, Emotional, Social, and School Functioning domains. It contains a parent proxy report for children aged 2 years and over and will be used in the study to derive Quality-Adjusted Life Year (QALYS) for the health economic evaluation. Internal consistency for the parent version is acceptable (α = .86) and has demonstrat4ed discriminant validity. This will be completed at baseline, 4-month and 12-month follow-up [33].
EuroQol-5D	Captures parental and caregiver perspective on their health status at baseline, 4-month and 12-month follow-up which will be used in the economic evaluation [34].
Client Satisfaction Questionnaire	Measures parent intervention acceptability [35]. The questionnaire will allow parents to provide feedback about the intervention during the 4 month follow-up by commenting on their satisfaction with and experience of the intervention, including ease of use, format and helpfulness. It has been specifically developed for research in SSTP and has high internal consistency (α = .92) [30].
Case Report Forms (CRF)	To collect sociodemographic and clinical information about comorbidities.

**Table 3 Tab3:** Schedule of assessments

Visit no	1	2	3	4
Tasks	Screening	Baseline assessment*	4 month follow-up	12 month follow-up
Allowed deviation window	n/a	+/ week	+/− 4 weeks	+/− 4 weeks
Informed consent (screening)	x			
Assessment of eligibility criteria	x	x		
Adaptive Behaviour Assessment Schedule (< 69)	x			
Research assessments minimum 1 week, maximum 4 weeks after screening)				
Informed consent (research)		x		
Mullen Scales of Early Learning		x		
CRF		x		
Preschool CBCL		x	x	x
Parent-child observation and FOS-RIII		x	x	x
C-TRF		x	x	x
GHQ-12		x	x	x
QRS-F short form		x	x	x
Caregiving Problem Checklist-Difficult Child Behaviour scale		x	x	x
PSOC		x	x	x
CA-SUS		x	x	x
Client Satisfaction Questionnaire			x	
Peds-QL		x	x	x
EQ-5D		x	x	x

*: at baseline, all assessments will be carried out prior to randomisation

The primary outcome measure is the parent completed Child Behaviour Checklist (CBCL; 24) at 12 months. The CBCL is a robust and widely used questionnaire which measures child behaviour and has been previously used in clinical trials and epidemiological studies of children with ID [36, 37]. Secondary outcomes include direct observations of parent-child interactions, parental health, stress and competence, service use and health related quality of life (Table 2).

### Sample size

A sample of 258 children (SSTP: 155 children, TAU: 103 children) will allow us to detect a low to moderate (standardised) effect size of 0.40 for the primary outcome at the 5% significance level, with 90% power. This is equivalent to detecting a clinically meaningful difference between the two treatment groups of 8 points, assuming a standard deviation of 20. This calculation is based on baseline-adjusted (ANCOVA) analysis assuming a correlation of 0.5 between baseline and follow-up measurements. In addition, the calculation has been adjusted for therapist clustering, assuming an intra-class correlation of 0.05, average group size of 7, and an anticipated drop-out of 10%.

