### Statistical methods

#### Analysis of primary outcome

A consort flow diagram [40] is used to describe the progress of participants through the study and the follow-up at different time points. Descriptive analyses (means, standard deviations, relevant quantiles and proportions) will be used to summarise the characteristics of the children in each study arm. A comparison of baseline characteristics will be performed to assess whether balance has been achieved; any notable imbalances may lead to additional adjusted analyses for continuous outcomes.

The primary analysis of the CBCL score at 12 months will use mixed models to perform an individual level analysis and will follow Roberts and Roberts (2005) [41] in adjusting for therapist clustering in the intervention arm only (random coefficient model). The final model will also adjust for baseline CBCL score and randomization stratification factors (centre, level of ID) using fixed effects. All modelling assumptions will be checked and a sensitivity analysis will be performed relaxing the heteroscedasticity assumption. Significance will be considered at the 5% level and confidence intervals with be at the 95% level.

Additional analyses will be performed for the secondary outcomes. Continuous outcomes will be analysed using a similar modelling approach to that described for the primary outcome, but for binary outcomes we shall use logistic mixed models [42]. The amount of missing data in each trial arm will be reported and we will investigate its impact on the balance achieved by randomisation. We will also explore whether missingness is associated with any participant characteristics, using descriptive comparisons and tests as appropriate. This may lead to further adjusted analyses. Stata 15 and R 3.6.0 or above will be used to perform the analyses.

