#### Trial status

Participant recruitment in this study commenced in September 2017. A 10-month internal pilot tested feasibility, acceptability and recruitment at all sites, using the full baseline and eligibility and follow-up assessment battery for all cases and the start-up of SSTP delivery to some of the participants. The progression criterion was that the rate of recruitment between months 5–14 should be at least 70% of the rate expected (no fewer than 8 children per month). This was achieved and the Trial Steering Committee advised NIHR to proceed to the full trial. The study is actively recruiting. To date, 190 participants have been randomised into the study and 19 groups have been completed.

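### The sample size and the primary model both name the therapist as the cluster, but the 90% power was calculated with clusters of 7, which fits a parent group and not the caseload of eight therapists

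*Protocol article*

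**What the plan says.** All statements are in the protocol article.

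- **Sample size:** "A sample of 258 children (SSTP: 155 children, TAU: 103 children") is said to detect a "low to moderate (standardised) effect size of 0.40 for the primary outcome" "at the 5% significance level, with 90% power". In points this is a "difference between the two treatment groups of 8 points, assuming a standard deviation of 20". The calculation is a baseline-adjusted one with correlation 0.5, "adjusted for therapist clustering, assuming an intra-class correlation of 0.05, average group size of 7", and 10% drop-out.
- **Treatment fidelity:** "Each therapist (eight: two per centre) responsible for delivering SSTP" has been trained and is supervised, so the number of therapists is eight.
- **Analysis of primary outcome:** the mixed model works by "adjusting for therapist clustering in the intervention arm only (random coefficient model"), with fixed effects for baseline CBCL, centre and level of ID.
- **Interventions:** SSTP consists of six group sessions and three individual contacts.
- **Trial status:** at the time of writing, "190 participants have been randomised into the study and 19 groups have been completed".

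**The concern.** The sample size names one unit, the therapist, and takes its cluster size from another, the group. Clusters of 7 would need about 155/7 = 22 therapists, and the trial has eight. The primary model then names the therapist again. As written, either the 90% power or the named random effect is wrong.

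Two things depend on which it is. The random effect sets the standard error and the degrees of freedom of the primary result, and eight clusters can give a different confidence interval from about 22. If the unit is left ambiguous, it could be settled after the data are seen. The power figure also bears on how a null result is read. The Discussion lists adequate power as a strength, and the Dissemination policy anticipates that a negative trial might be taken to mean that usual care is as effective as the manualised programme.

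**Working it through.** **Inputs.** From Sample size: difference 8, SD 20, correlation 0.5, ICC 0.05, cluster size 7, drop-out 10%, 155 and 103 children. From Allocation: ratio 3:2. From Treatment fidelity: eight therapists. Assumed: a two-sided 5% test, since the sidedness is not stated, and equal caseloads.

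**Step 1. Reproduce the stated sample size.**
- Residual variance after baseline adjustment: 20² × (1 − 0.5²) = 300.
- Design effect in the SSTP arm only: 1 + (7 − 1) × 0.05 = 1.30.
- TAU n = (1 + 1.30/1.5) × 300 × (1.960 + 1.282)² / 8² = 91.9.
- Allowing for drop-out: 91.9/0.9 = 102.2, rounded up to 103. Then 103 × 1.5 = 154.5, rounded up to 155. The total is 258, as stated.

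Applying the design effect to both arms gives about 296, which does not match. The stated figure therefore came from clusters of 7 in the SSTP arm only.

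**Step 2. What 7 can refer to.**
- Per therapist: 155/8 = 19.4 allocated, and 139.5/8 = 17.4 after 10% drop-out.
- Per group, from Trial status: 190 × 0.6 / 19 = at most about 6 SSTP families per completed group.

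A size of 7 fits the parent group and not the therapist.

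**Step 3. Power for each unit.** Retained children: 155 × 0.9 = 139.5 and 103 × 0.9 = 92.7. The variance of the difference is 300 × (DE/139.5 + 1/92.7), where DE = 1 + (m − 1) × ICC. Normal-approximation power is Φ(8/SE − 1.960). The t version uses a noncentral t with Satterthwaite df, taking k − 1 df for the SSTP component (k clusters) and 91.7 for TAU.

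| Cluster | ICC | m | DE | SE | Power, normal | Power, t (df) |
|---|---|---|---|---|---|---|
| Parent group | 0.05 | 7 | 1.30 | 2.456 | 90.3% | 89.5% (69) |
| Eight therapists | 0.05 | 17.4 | 1.82 | 2.675 | 84.9% | 81.6% (22) |
| Eight therapists | 0.03 | 17.4 | 1.49 | 2.539 | 88.3% | 85.8% (26) |
| Eight therapists | 0.02 | 17.4 | 1.33 | 2.469 | 90.0% | 87.9% (29) |
| Eight therapists | 0.01 | 17.4 | 1.16 | 2.396 | 91.6% | 90.0% (33) |

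Like for like at ICC 0.05, moving from group to therapist costs about 5 percentage points by the normal approximation (90.3 to 84.9) and about 8 by t (89.5 to 81.6).

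**Step 4. Difference detectable with 90% power (normal approximation).** This is (1.960 + 1.282) × SE: 3.242 × 2.456 = 8.0 points for groups of 7, and 3.242 × 2.675 = 8.7 points for eight therapists at ICC 0.05.

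**The case against.** The best defence is that the authors meant groups. The sample-size sentence itself speaks of group size, delivery is in groups, and the completed groups are close to 7 in size. On that reading therapist clustering is shorthand for clustering by therapist-led group, the arithmetic is right and no power is lost. That stands as far as the planning figure goes. It does not clear the analysis section, which names the therapist and so omits the group as a level.

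A second defence is that 0.05 was paired with clusters of 7, and the article gives no separate ICC for caseloads of about 17. This also stands: the loss is conditional, and at a therapist ICC of 0.02 or below 90% survives by the normal approximation (0.01 by t). Against that, the article does attach 0.05 to therapist clustering, so 0.05 is the natural value at which to test the statement.

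A third is that the full random-effects specification may sit in an SAP that is not shown. It may, but the point is not that detail is missing. The article names one unit in two places and pairs it with a size that its own therapist count rules out.

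Two stronger readings are tempting and should not be drawn. A reader might infer that the trial is simply underpowered, but that follows only if the therapist is the intended cluster and its ICC is near 0.05. A reader might also infer from two therapists per centre that they lead groups in pairs, leaving four clusters and much lower power. Nothing in the article says that therapists co-lead, so no figure is given for that case.

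**Conclusion.** The point holds as an inconsistency between the cluster planned for and the cluster named for analysis. The sample-size arithmetic is correct for clusters of 7.

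- If the parent group is the cluster, power is about 90% as stated, and the primary model is misnamed.
- If the therapist is the cluster, power at ICC 0.05 is about 82-85% and not 90%. It ranges from 81.6% to 90.0% by t (84.9% to 91.6% by the normal approximation) as the ICC falls from 0.05 to 0.01.

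The therapist figures assume equal caseloads, 10% drop-out and eight therapists throughout. Unequal caseloads would lower power, and additional or replacement therapists would raise it. The 95% confidence interval already planned will show whether 8 points is excluded, which limits the risk of over-reading a null result, provided the interval comes from the right random effect. This is a should-fix.

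**What to change.** Name one clustering unit in both Sample size and Analysis of primary outcome, and in any SAP, before database lock. Either option is acceptable:

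1. **Therapy group.** Fit a random effect for group in the SSTP arm only, state that ICC 0.05 and size 7 refer to groups, and keep the 90% power statement. Fit therapist clustering as a sensitivity analysis. A further random level for eight therapists in the primary model is a debatable choice and is not needed.
2. **Therapist.** Keep the model as named, replace the cluster size of 7 with the expected caseload, and restate power as about 82-85% at ICC 0.05, with the range over smaller ICCs shown.

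The sample size of 258 should stay as it is. The cost is wording, recording each child's group and therapist in the analysis dataset, one sensitivity model under option 1, and a less favourable power statement under option 2.
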